### Phase 1: Intervention Development

#### Panel Development

We convene the rural CAP using the “broad community” model to capture participants’ opinions about vaccination [20]. We work directly with Cooperative Extension Educators at Oklahoma State University (OSU) to identify and partner with (1) key stakeholders (eg, community leaders) and (2) members of the community for panel development. Cooperative Extension is a key branch of the land-grant system and includes community outreach and health-related engagement with populations across the state, including rural adults [21]. We use purposive sampling to identify, with educators’ input, and recruit key partners within rural counties with the lowest vaccination rates at the time of recruitment. We recruit a minimum of two individuals in the bottom 10% of vaccinated counties across Oklahoma to participate in the CAP. Our target total sample size for phase 1 is 15-20 CAP participants in order to achieve this benchmark, which is consistent with existing recommendations in qualitative research [22].

#### Eligibility Criteria

Inclusion criteria include being ≥18 years of age, residing in a target county and being identified as a key stakeholder, and willingness to provide informed consent and complete a semistructured interview. There are no exclusion criteria.

#### Interview Procedure

We conduct one-on-one semistructured interviews with each participant (see Multimedia Appendix 1). Interviews include open-ended questions to gauge barriers and facilitators to vaccination. To promote the diversity of opinions, research personnel are trained in using open-ended questions that are developed with empathy-driven, user-centered principles [23] and in using MI-consistent prompts (eg, “Please tell us about the impressions of vaccines in your community” or “Please share your experience with vaccinations”). For individuals who express vaccine resistance, questions focus on their perspectives (eg, “Tell me what you don’t like about vaccines”) and hypotheticals (eg, “Imagine you were to get the vaccine, what would those circumstances look like?”). For those who have been vaccinated, questions similarly focus on community perceptions and participants’ own experiences (eg, “Tell me about your decision to get the vaccine”). Lastly, questions also center on mHealth (eg, “Imagine you were to use an app to help you make health care decisions – what would that look like to you?”). All interviews are about 30-45 minutes via phone, video call, or in-person if preferred. Interviews are recorded and transcribed verbatim for analysis.

#### Qualitative Data Analysis

Interviews conducted with the CAP are transcribed verbatim and triple-coded by 3 separate members of the research team to inductively identify themes classified broadly as barriers to and facilitators of receiving the COVID-19 vaccine as well as the use of mHealth using content analysis. In addition, all transcripts are reviewed for identification of SCT constructs and opportunities for the use of MI relational skills, technical skills, and existing empirical evidence [24,25]. This approach uses a reflexive strategy to integrate three different researchers’ perspectives into the data set (eg, experience in SCT versus MI) [26]. Coding matrices are used to match MI- and SCT-specific elements to barriers to and facilitators of vaccination to design potential mHealth-specific messages. Discrepancies in coding are discussed to achieve intercoder agreement, and inductive thematic saturation is achieved at the time of analysis by iteratively reviewing the emergence of new themes during triple coding [27]. If saturation is not achieved in that new themes emerge at the time of analysis that are not well integrated into the codebook, additional community members will be recruited to complete interviews (maximum total n=20) [28]. The final data set is entered into the NVivo software (Lumivero, LLC) package [29]. Codes are organized into barriers and facilitators; other categories can be created as they emerge during the coding process.

### Phase 2: Pilot RCT

#### Participant Recruitment

We leverage multiple recruitment strategies in an intentional effort to reach historically underrepresented areas across Oklahoma. For phase 2, we partner with OSU Cooperative Extension and TrialFacts to target primarily rural counties to recruit a total of 60 participants. Around 60 participants are selected as consistent with recommendations for pilot studies, taking into consideration the focus on evaluating feasibility, as well as practical restraints [30]. TrialFacts is a participant recruitment service company that provides targeted recruitment of specific populations of interest.

#### Eligibility Criteria

Eligible adults are (1) aged ≥18 years, (2) living in a rural area (based on Rural-Urban Commuting Area codes; rural, codes 4-10) [31,32], (3) self-report of never having received any dose of a SARS-CoV-2 vaccine, (4) able to speak English, and (5) able to provide written informed consent. Exclusion criteria include (1) a cognitive or other disability that inhibits smartphone use, (2) inability to participate because of medical or psychiatric conditions diagnosed by a physician or clinician, or (3) enrollment in other COVID-19 research.

#### Procedure

RCT participants (N=60) are randomized to one of the 3 treatment groups using simple randomization in the REDCap (Research Electronic Data Capture; Vanderbilt University) program [33,34]. These groups include standard MI (SMI; n=20), intensive MI (IMI; n=20), or mHealth-based MOTIVACC (n=20). SMI consists of one MI session at least 20 minutes in length [35-38] delivered by a trained counselor at the baseline and provision of printed self-help materials. IMI consists of the SMI component plus 3 additional MI sessions delivered by a trained counselor via telephone or video calls at weeks 2, 4, and 6 post enrollment. MOTIVACC consists of an empathy-driven, fully automated, smartphone-based MI program that involves proactive, interactive, and individually tailored messages, plus some embedded images or videos, delivered by our Insight app [39]. MOTIVACC will begin immediately after enrollment and data collection and continue for an 8-week period (about 2-5 messages or questions per day, depending on participants’ interaction and responses). The intervention content in all groups is adapted from the team’s previous work and existing empirical evidence for in-person MI [25], is informed by Phase 1 outcomes, and is designed to tap SCT mechanisms. Insight for Android is used and any participants enrolled in MOTIVACC who do not have an Android phone will be loaned one for the duration of the study. All participants are followed up at week 8 post enrollment via individualized REDCap survey links sent via email [33,34].

#### Outcomes and Measures

Primary assessments (self-reported data) are conducted at baseline (after completing informed consent) and 8 weeks (after completion of the intervention if applicable). Additional data regarding the completion of the intervention contacts is recorded at the time of delivery in REDCap by study personnel (ie, for MI) or consistently and automatically in Insight (ie, for MOTIVACC). Table 1 displays the assessments and measures. The primary RCT outcomes are positive changes in the vaccine hesitancy scale [40,41] and intention to obtain the vaccine [42,43]. The secondary outcome is actual vaccination.

**Table 1 table1:** Trial assessments at baseline and 8-week follow-up.

Variable type	Measure
Descriptors and potential moderators	Demographics [44], health literacy [45] COVID-19–related experience [46,47], health conditions, or diagnoses
Feasibility/ Adherence to MOTIVACC^a^	Numbers of messages/images/videos opened and completed; weekly EMAs^b^ opened and completed
Social Cognitive Theory– and motivational interviewing–related mechanisms	Expectations (eg, vaccination benefits or consequences of not being vaccinated) [42,48] Ambivalence regarding vaccination [49,50] Behavioral capability (eg, perceived barriers) [48]
Qualitative, open-ended assessment	An in-app participant-initiated assessment—“Share your thoughts with us”—with an open text field to capture the participant’s thoughts and feelings
Primary outcomes	Vaccine hesitancy and confidence [40,41] Intention to receive the vaccines [42,43]
Secondary outcomes	SARS-CoV-2 vaccine receipt

^a^MOTIVACC: mHealth-based motivational interviewing intervention to promote SARS-CoV-2 vaccination.

^b^EMAs: Ecological momentary assessment.

#### Compensation

All clinical trial participants receive one US $30 gift card as compensation for completion of baseline and 8-week follow-up data collection.

### Statistical Analysis

This pilot study was designed to test feasibility, acceptability, and preliminary efficacy; thus, existing recommendations regarding sample sizes for pilot studies were used [30] versus a formal power calculation. Descriptive statistics will be used to assess the feasibility and acceptability of MOTIVACC, including the proportion of individuals who met inclusion criteria, the proportion of eligible participants who agreed to participate, the proportion of prescheduled events (intervention messages and interactive open-ended questions) delivered, viewed, or completed, and attrition rate at 8-week follow-up. The preliminary efficacy of IMI or MOTIVACC vs. SMI in changing participants’ vaccine hesitancy and uptake intention will be evaluated using generalized linear mixed models, controlling for selected covariates such as sex and education level. Secondary outcomes will be examined using log-binomial regression with an intent-to-treat approach (ie, missing=no vaccine receipt) to compare the effect of IMI or MOTIVACC on the dichotomous 1st-dose vaccine receipt outcome at 8 weeks post enrollment. As aforementioned, given the preliminary nature of the RCT, we do not expect to have sufficient power for full hypothesis testing. For missing data, we will consider a multiple imputation approach based on participants’ demographics at baseline to account for potential missing-at-random mechanisms. We also will explore pattern-mixture and selection models to account for potential (and likely) missing-not-at-random mechanisms [51].

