## Introduction

Throughout the COVID-19 pandemic, rural populations have had lower rates of SARS-CoV-2 vaccination, increased vaccine hesitancy, and higher risks of morbidity and mortality associated with active infection than urban populations [1]. Increased likelihood of vaccine hesitancy has been associated with rural residence, low household income, and less education [2]. While some strides have been made in rural vaccination, it has been estimated that those who remain unvaccinated and currently reside in rural areas are less likely to consider vaccination (eg, will “definitely not” get vaccinated) [3]. In Oklahoma specifically, as of May 10, 2023, 68% of Oklahomans aged 18–35 years and 57% of Oklahomans aged 36-49 years had not received any dose of a SARS-CoV-2 vaccine [4]. However, in urban counties, 76%-95% of adults had received at least one dose, while the rates in rural counties ranged from 37%-65% [5]. Further, it has been estimated that as many as two-fifths of rural Oklahoman residents are hesitant to receive the vaccine [6].

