Health communication has been consistently identified as a key element in promoting vaccine uptake and addressing vaccine hesitancy. Historically, approaches taken to communication vary [7] but may focus on attempts to craft persuasive informational messages [8]. The effect of these messages is likely minimized, as many individuals who are vaccine-hesitant perceive the source of information (eg, health care providers) as misinformed [8], thus a fundamental shift in the purpose of vaccine-related communication is essential. Such approaches may instead focus on honoring individual autonomy and navigating information and perceptions of information, versus relaying of information itself [9]. Data also suggest the advantage of using messages that emphasize the personal benefits of vaccination rather than prosocial benefits in reducing vaccine hesitancy; however, this may differ according to individual values [10]. Thus, it is critical to align individual priorities with intervention content, a key feature of motivational interviewing (MI) [11]. No studies have examined the effects of MI on vaccination rates among adults most vaccine-hesitant. MI has documented efficacy in vaccine-hesitant parents (eg, child HPV vaccines): vaccine intention rose by 12%, hesitancy decreased by 40% [12], and vaccine coverage in infants increased by 3.2%, 4.9%, and 7.3% at 3, 5, and 7 months of age, respectively [13]. MI has also been used to promote HPV vaccination in high-risk adults with promising results [14], but not necessarily in those who are vaccine-hesitant. While promising, MI delivery can be laborious, limiting scalability. Alternatively, mobile health (mHealth)–based interventions have been used to promote vaccination [15]. Thus, integrating MI into automated platforms is essential for scalability to improve public health.

The World Health Organization (WHO) acknowledges mHealth as a cost-effective, scalable, and sustainable way to improve public health [16]. A limiting factor in MI’s effectiveness is scalability due to the intensity of provider training and evaluation. Further, smartphone ownership in the United States increased from 35% in 2011 to 90% in 2023 [17] with similar rates across urban and rural groups (91% and 87%, respectively). Near-universal smartphone ownership provides an ideal yet untapped mechanism to deliver MI-based vaccine interventions to rural populations.

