## Results

This project is funded by the Oklahoma Shared Clinical & Translational Resources Pilot Grant Program, which is funded by the National Institute of General Medical Sciences, a part of the National Institutes of Health (U54GM104938). The study is approved by the institutional review boards of both University of Oklahoma Health Sciences and OSU. As of April 2024, data collection for phase 1 was complete with a total of 16 individuals recruited to participate in the CAP. Qualitative data analysis for phase 1 contributed to the MOTIVACC intervention development and testing (Figure 1). As of December 2024, the planned recruitment goal has been met (ie, n=60, 20/arm) and follow-up assessments are underway. The CONSORT flow diagram is shown in Figure 2, and the SPIRIT checklist is uploaded in Multimedia Appendix 2.

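### Log-binomial regression for first-dose receipt gives no finite risk ratio for any contrast with an empty arm, which is likely with 20 per arm if uptake is about 5% or less and still a real risk at 10%

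*Protocol article*

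**What the plan says.** The Statistical Analysis section of the protocol article fixes the model: "Secondary outcomes will be examined using log-binomial regression". The same sentence, under an intent-to-treat label, counts anyone with missing follow-up as not vaccinated. The endpoint is the "dichotomous 1st-dose vaccine receipt outcome at 8 weeks post enrollment". The Results section reports that "the planned recruitment goal has been met (ie, n=60, 20/arm"), and the Phase 2 Eligibility Criteria require "self-report of never having received any dose of a SARS-CoV-2 vaccine".

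The comparator is stated for the primary outcomes: "The preliminary efficacy of IMI or MOTIVACC vs. SMI". The sentence on vaccine receipt does not repeat it, so SMI as the reference arm is assumed here. That sentence also lists no covariates; sex and education are named only for the mixed models on hesitancy and intention. No expected uptake rate is given anywhere for this population. The authors give no formal power calculation and say that they do not expect enough power for hypothesis testing.

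**The concern.** A log-binomial model estimates the logarithm of each arm's event probability. If an arm has no events, its estimated probability is zero, the logarithm does not exist, and the risk ratio for any contrast that uses the arm is zero, infinite or undefined. Software may still print a very large coefficient and standard error, which mean nothing.

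The design makes empty arms plausible: 20 people per arm, nobody vaccinated at entry, an 8-week window, and every dropout counted as unvaccinated. The Introduction adds that "those who remain unvaccinated and currently reside in rural areas are less likely to consider vaccination". At stake is the comparison of actual vaccination between arms, which is the part of the preliminary efficacy evidence closest to the trial's purpose and an input to the larger trials that the Conclusion foresees.

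**Working it through.** The article states no uptake rate, event count or power for this outcome, so there is no figure of its own to reproduce.

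**Inputs.** n = 20 per arm and three arms (Results); first-dose receipt at 8 weeks with missing counted as no (Statistical Analysis); SMI as reference (assumed). Uptake p is an assumption, shown as a range and taken as equal in all arms unless stated.

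**Step 1: why an empty arm breaks the model.** In the arm-only model the risk ratio is the ratio of observed proportions. With a events of 20 in SMI and b of 20 in the other arm, log RR = log(b/a), and its Wald standard error is √(1/a − 1/20 + 1/b − 1/20). If a or b is 0, neither quantity is finite.

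**Step 2: how often this happens.** The chance that one arm is empty is q = (1 − p)^20. A given contrast with SMI includes an empty arm with chance 1 − (1 − q)². At least one of the three arms is empty with chance 1 − (1 − q)³. At p = 5%, q = 0.95^20 = 0.358, so the chances are 1 − 0.642² = 0.588 and 1 − 0.642³ = 0.736.

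| Assumed uptake | Expected events per arm | SMI empty | Given contrast includes an empty arm | At least one arm empty |
|---|---|---|---|---|
| 2% | 0.4 | 67% | 89% | 96% |
| 5% | 1.0 | 36% | 59% | 74% |
| 8% | 1.6 | 19% | 34% | 47% |
| 10% | 2.0 | 12% | 23% | 32% |
| 15% | 3.0 | 4% | 8% | 11% |
| 20% | 4.0 | 1% | 2% | 3% |
| 30% | 6.0 | 0.1% | 0.2% | 0.2% |

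An empty SMI arm spoils both contrasts; an empty active arm spoils only its own. Both contrasts are also lost if both active arms are empty while SMI is not. That adds (1 − q)q²: 0.642 × 0.358² = 8 percentage points at 5% uptake, and 0.878 × 0.122² = 1 point at 10%.

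**Step 3: unequal uptake.** With 5% in SMI and 10% in each active arm, at least one arm is empty with chance 1 − (1 − 0.358)(1 − 0.122)² = 0.505. With 10% and 20% it is 14%.

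**Step 4: dropouts counted as no.** If 20% drop out (an assumption) independently of uptake, true uptake of 5% becomes an effective 4% and the chance of at least one empty arm rises from 74% to 83%. At 10% (effective 8%) it rises from 32% to 47%.

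**Step 5: check by simulation.** In 1,000 simulated trials per scenario, with arm alone in the model, the fit failed in 73% at 5% uptake, 33% at 10% and 3% at 20%. These were exactly the trials with an empty arm; whenever every arm had an event, the model fitted.

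**Step 6: what the alternative gives.** Take 0/20 in SMI and 2/20 in an active arm. The Wilson limits are 0 to 0.161 and 0.028 to 0.301. The Newcombe interval for the difference of 0.100 runs from 0.100 − √((0.100 − 0.028)² + (0.161 − 0)²) = −0.077 to 0.100 + √((0.301 − 0.100)² + (0 − 0)²) = 0.301, about −8 to +30 percentage points. The log-binomial fit gives no finite ratio for the same data.

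**The case against.** **Uptake might not be rare.** The Introduction's remark is comparative and carries no rate, and all three arms receive some form of motivational interviewing. At 20% uptake the chance of an empty arm is 3%, and at 30% it is 0.2%. This stands: the size of the problem is conditional. The nearest figures in the article are that "vaccine coverage in infants increased by 3.2%, 4.9%, and 7.3% at 3, 5, and 7 months of age". At uptake of 3.2%, 4.9% and 7.3% the chance of at least one empty arm would be 89%, 75% and 53%, but those are gains in another population and indicate scale at most.

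**The authors already concede low power.** Low power means a wide interval. For example, 1/20 versus 2/20 gives a risk ratio of 2.0 with a 95% Wald interval of 0.20 to 20.3. An empty arm leaves no finite estimate at all, and the caveat does not cover that.

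**The article names no interval method.** A profile-likelihood interval from the same model can still give a finite bound on one side when one arm of the contrast is empty. This stands, so the claim about intervals is confined to Wald intervals. The point estimate is still not finite.

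**Stronger readings that a reader might infer.** Three go beyond the documents.
- That the model will fail to converge because of sex and education: no covariates are stated for this model, and without them it fails only when an arm is empty.
- That the plan has no fallback for sparse data: such a rule commonly sits in a statistical analysis plan, which is not shown. The point rests on the stated choice of model.
- That the outcome will probably yield no estimate at all: SMI is empty in 36% of trials at 5% uptake and 12% at 10%, so losing both contrasts is the likelier result only at very low uptake.

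**Conclusion.** The concern holds in a conditional form. The stated model suits this outcome poorly, because with 20 per arm a contrast with SMI has no finite risk ratio in 59% of trials at 5% uptake and 23% at 10%. At 20% uptake the figure is 2% and the problem largely disappears. The result assumes equal uptake across arms and SMI as the reference, and rests on an uptake range that the article does not supply. The never-vaccinated rural population, the short window and the counting of dropouts as unvaccinated all point towards the lower end.

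Severity is modest. Vaccine receipt is a secondary outcome in a pilot that disclaims hypothesis testing, no primary result or sample size depends on it, and counts per arm can be reported whatever happens.

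**What to change.** In the Statistical Analysis section, make the main analysis of vaccine receipt the number and proportion vaccinated in each arm, with the unadjusted risk difference of IMI versus SMI and of MOTIVACC versus SMI and a Newcombe or Miettinen-Nurminen 95% interval (one method, named in advance). Report a log-binomial risk ratio only as a supplement, and only if every arm has at least one event. If Firth-penalised or exact logistic regression is used, label the result as an odds ratio, because it is not the risk ratio that the log-binomial model targets.

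The change is one of wording. It should be made before receipt is tabulated by arm; the article describes follow-up as still underway in December 2024. The cost is that the main result is no longer a model-based or covariate-adjusted risk ratio. The proposed interval remains valid if uptake proves higher, so nothing is lost should the assumption of low uptake be wrong.

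### Counting missing vaccine receipt as 'no' is a single-imputation assumption, not intent-to-treat, and biases the risk ratio if week-8 response differs by arm and some non-responders were vaccinated

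*Protocol article*

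**What the plan says.** All places are in the Methods of the protocol article.

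- **Outcome.** Outcomes and Measures gives the rank: "The secondary outcome is actual vaccination". Statistical Analysis defines it as the "dichotomous 1st-dose vaccine receipt outcome at 8 weeks post enrollment".
- **Analysis rule.** Statistical Analysis specifies "log-binomial regression with an intent-to-treat approach (ie, missing=no vaccine receipt".
- **Data source.** Outcomes and Measures: "Primary assessments (self-reported data) are conducted at baseline (after completing informed consent) and 8 weeks". Procedure: "All participants are followed up at week 8 post enrollment via individualized REDCap survey links sent via email". Table 1 lists receipt among the assessments at these visits. No registry or medical-record source is stated.
- **Contact by arm (Procedure).** For standard MI, "SMI consists of one MI session at least 20 minutes in length", given at baseline. Intensive MI adds "3 additional MI sessions delivered by a trained counselor via telephone or video calls at weeks 2, 4, and 6 post enrollment". MOTIVACC sends roughly two to five app messages or questions a day for the whole 8 weeks.
- **Other missing-data methods.** Statistical Analysis will consider multiple imputation from baseline demographics. It continues: "We also will explore pattern-mixture and selection models to account for potential (and likely) missing-not-at-random mechanisms". Neither method is tied to a particular outcome.

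**The concern.** The rule raises three problems.

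**The label.** Intent-to-treat settles which arm a participant is counted in. It does not say what value a missing outcome takes. Joining the two lends a strong assumption the standing of a design principle, and a reader of the results may not see that an assumption was made.

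**The estimate.** Every participant who does not answer the week-8 email is recorded as unvaccinated. Standard MI, the natural reference arm, has no scheduled contact between the baseline session and that email, while the other two arms are contacted until week 6 or week 8. Response that differs by arm is therefore foreseeable. Where it does, and where some non-responders were in fact vaccinated, part of the apparent effect on receipt is an effect on survey response. The model also counts the filled-in values as observed, so its standard error carries none of the uncertainty about them.

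**The later sentences.** Once missing is set to 'no', no missing receipt values remain for imputation or pattern-mixture models to handle. Either those methods do not apply to receipt, which then has no sensitivity analysis, or they do apply and their relation to missing=no is unstated.

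Receipt is the trial's only behavioural outcome, and the Conclusion section expects the results to inform later fully powered trials. What is at stake is the effect estimate carried forward.

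**Working it through.** **Inputs from the article.** 20 participants per arm, 3 × 20 = 60; missing=no for receipt; the same emailed survey in all arms. The article gives no power calculation, vaccination rate, response rate or expected attrition, so there is no figure of its own to reproduce.

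**Assumed quantities, shown as a range.**
- r: week-8 response rate, in a more-contacted arm (T) and in standard MI (C).
- p: true vaccination rate, the same in both arms, so the true risk ratio is 1.00.
- s: vaccination rate among responders.
- k: vaccination rate of non-responders divided by that of responders, taken as the same in both arms.

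**Formulas.** Overall vaccination is p = s[r + (1−r)k]. Under missing=no the recorded rate is r × s, so

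RR(missing=no) = r_T[r_C + (1−r_C)k] / {r_C[r_T + (1−r_T)k]}.

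Among participants with known status only,

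RR(observed) = [r_C + (1−r_C)k] / [r_T + (1−r_T)k].

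Neither depends on p.

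**Results.**

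| k | Missing=no, 90% vs 70% | Missing=no, 90% vs 60% | Observed only, 90% vs 70% |
|---|---|---|---|
| 1 | 0.90/0.70 = 1.29 | 0.90/0.60 = 1.50 | 1.00 |
| 0.5 | (0.90×0.85)/(0.70×0.95) = 1.15 | (0.90×0.80)/(0.60×0.95) = 1.26 | 0.85/0.95 = 0.89 |
| 0.25 | (0.90×0.775)/(0.70×0.925) = 1.08 | (0.90×0.70)/(0.60×0.925) = 1.14 | 0.775/0.925 = 0.84 |
| 0 | 1.00 | 1.00 | 0.70/0.90 = 0.78 |

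Also at k = 1: 85% vs 75% response gives 1.13; equal response gives 1.00; and 70% in the new arm vs 90% in standard MI gives 0.70/0.90 = 0.78, a bias against the new arm.

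**Simulation check** (p = 0.20, k = 1). Missing=no gave 1.28 for 90% vs 70% and 1.49 for 90% vs 60%; observed cases gave 0.99 in both.

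**In participants.** At p = 0.20, k = 1 and 90% vs 70% response, expected recorded vaccinations are 20×0.20×0.90 = 3.6 and 20×0.20×0.70 = 2.8, a difference of 0.8. Expected missing are 20×0.10 = 2 and 20×0.30 = 6, so in standard MI the missing would outnumber the recorded events.

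**False positives.** Enumerating Fisher's exact test at 20 per arm and p = 0.20 (used as a check; the plan's model is log-binomial) gives a 5%-level rejection rate of 2.8% for 90% vs 70% and 3.7% for 90% vs 60%, against 2.3% with complete data. The damage is to the estimate more than to the error rate.

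**The case against.** The strongest defence has four parts.

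1. **Missing=no may be close to the truth.** Participants have never had a dose and are followed for only 8 weeks. If non-responders almost never vaccinate, the bias is small, and it is nil at k = 0. This stands. A reader might infer that the expected risk ratio simply equals the ratio of response rates. That holds only at k = 1, and nothing in the article supports k = 1 over a lower value.

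2. **The direction is not known.** All arms receive the same link and the same gift card, and daily messages over 8 weeks may tire participants. This also stands. A reader might infer that the rule predictably favours the more-contacted arms. The article gives no response rates, and if standard MI responded better the bias would run the other way.

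3. **Analysing known status only is no safe replacement.** It has the mirror-image bias: 0.78 at 90% vs 70% when k = 0. The article itself regards missingness not at random as likely, which counts against making observed cases the main estimate. This stands, and it shapes the fix.

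4. **The article already names other methods, and a condensed article may leave their details to the analysis plan.** This stands in part. Missing detail is not the complaint. The article does fix a rule for receipt, labels it wrongly, and names alternatives that are only to be considered or explored, without linking them to this outcome.

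**Conclusion.** The point holds in a conditional form. Equating intent-to-treat with missing=no is wrong as written. The rule biases the risk ratio toward the better-responding arm if two conditions are met: response differs by arm, and some non-responders were vaccinated. At an assumed 90% vs 70% response with equal true receipt, the expected risk ratio runs from 1.00 (k = 0) through 1.15 (k = 0.5) to 1.29 (k = 1); with the response rates swapped it is 0.78 at k = 1. Whatever the direction, the standard error ignores uncertainty about the missing values.

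These sizes rest on assumed response rates, on k being equal in both arms, and on receipt having no source beyond the survey. If receipt were confirmed from records for everyone, the problem would largely disappear.

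A reader might also infer that the rule threatens the trial's main conclusions. The article does not support that: receipt is secondary, the pilot expects too little power for full hypothesis testing, and the false-positive rate barely moves at this size. Severity is moderate.

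**What to change.** 1. Delete the equation of intent-to-treat with missing=no. State that all randomised participants are analysed by assigned arm, and state the missing-data assumption separately.
2. Missing=no may stay as one analysis, labelled as an assumption.
3. Report week-8 response by arm beside the receipt result.
4. Commit to applying the multiple imputation and pattern-mixture analyses already named in Statistical Analysis to receipt, with randomised arm in the imputation model as well as baseline demographics.
5. Add a tipping-point table that varies the number of receipts among each arm's missing participants from none to all. With 2 and 6 missing, as in the example above, a two-arm comparison has 3 × 7 = 21 cells.
6. Draw a conclusion on receipt only if it is stable across these analyses.

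This is a cheap improvement: wording, one or two extra tables, and possibly a less definite conclusion on receipt. With few events per arm the imputation results will be imprecise, which is why the tipping-point table matters most. No new data are needed. The Results section reports follow-up still underway in December 2024; the change is most credible if fixed before outcomes are seen by arm.
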